#### Outcome measures:

The primary outcome will be

- Error rate as assessed by the validated ICECAP Tool (Imperial College Error Capture Tool) a validated multi-dimensional assessment of error

Secondary outcomes will be

- Time to complete the clinical scenario
- Successful completion of the clinical scenario - as assessed by simulation team
- Global assessment of team performance - assessed using the validated OTAS Tool (Observational Teamwork Assessment for Surgery) and T-SAW-C Tool (Teamwork Skills Assessment for Ward Care)
- Errors in PPE use - assessed according to Public Health England (PHE) guidance and number of visor failures (e.g., inadvertent removal, misting, contamination or obstruction of clinical care)
- Participant stress/cognitive load - assessed via the validated NASA Task Load Index (NASA-TLX) and State Trait Anxiety Index (STAI) Tools
- Usability / technology feedback questionnaire for those wearing the HL2

All questionnaire items and assessment tools listed above are provided in the attached documents. Participant responses will be collected at the time of study completion, and assessment of video recordings will be undertaken during the data analysis stage of the study

**Statistical analysis:** Standard descriptive data will be employed. Independent two-sample t-tests will be calculated for normal continuous data, including ICECAP and OTAS scores, and time-to completion data. The Wilcoxon-Mann-Whitney U test will be used to analyse TLX scores. Multivariate linear regressions will be calculated to control for potential confounders and to assess association. Within subject comparisons will also be made to assess how the technology influences individual performance.

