2. Advanced Life Support: All participants will be provided with a refresher instruction on core aspects of advanced life support according Resuscitation Council UK guidelines. Instruction provided will cover all knowledge and practical skills required to successfully complete each of the simulated clinical scenarios, including advanced airway skills. Clinical scenario protocols will be written by experienced simulation practitioners and based upon the guidelines for the management of in-hospital assessment and resuscitation of the critically unwell patient.

**Simulation study method:** The study will be conducted according to a randomised cross-over design. Participants will complete two simulated clinical resuscitation scenarios as part of a single half-day study session that will also include their standardised training. There will

be a wash-out period of at least 1 hour between each scenario. This is a deliberately pragmatic methodological approach that has been chosen to ensure sufficient participant recruitment and study completion given time demands on participants if the study were to be split across multiple sessions. Prior to commencing the first simulated scenario participants will be randomly assigned to one of two groups - standard care, or HL2 supported care - and will cross-over into the alternate group for the second scenario. The order of the test scenarios will be counterbalanced to mitigate any learning effects. The order of HL2/standard care will be determined by using sealed envelopes prior to starting the simulation. Participants will be required to undertake advanced airway skills in order to test the impact of HL2 on remotely supporting the delivery of vital clinical skills in high stress situations. The clinical scenarios will not be identical but will be based upon standardised clinical moulages undertaken for basic and advanced life support qualifications, and those undertaken by doctors in training as part of their core curriculum to ensure consistency, reliability and control for learning effects.

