The simulation will be undertaken in a specialist simulation lab at Imperial College London facilitated and led by experienced simulation practitioners. The research team will be solely responsible for capturing observational data. A high-fidelity adult patient simulator (Laerdal) will be used to simulate an unwell adult with COVID-19. Vital signs will be standardized and pre-programmed with an adjustable override feature controlled by the study investigators. Before the start of each simulation session, study investigators will provide information to the participants on the patient using a standardised clinical moulage, with instructions to follow during the case, and the roles of study participants defined prior to the start of the simulation. Simulated medications, fluids, and equipment will all be available. Full PPE will also be available to all participants in the scenario. All scenarios will be video recorded, and these will subsequently be assessed by two independent researchers.

We aim to enrol 30 individual participants into the study who will undertake a total of 60 clinical scenarios (30 as standard care, 30 as HL2 supported care). The study will take place in a single setting - the study team anticipate this will last a maximum of 2hrs to allow for consent, initial technical training and the completion of 2x clinical scenarios.

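### NASA-TLX and STAI are timed at study completion, after both scenarios, so workload and anxiety in each participant's first condition would be rated from recall

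*Protocol*

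**What the plan says.** The Outcome measures part of section 10 lists, among the secondary outcomes, "Participant stress/cognitive load - assessed via the validated NASA Task Load Index (NASA-TLX) and State Trait Anxiety Index (STAI) Tools". Below the list it gives the only timing for participant-reported data: "Participant responses will be collected at the time of study completion". The same sentence places the rating of the video recordings later, in the data analysis stage.

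The design, under Simulation study method in section 10, is a two-period cross-over. "Participants will complete two simulated clinical resuscitation scenarios as part of a single half-day study session", and each participant "will cross-over into the alternate group for the second scenario". Between the two there is a "wash-out period of at least 1 hour between each scenario".

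Other parts of the protocol bear on the use of these scores. The Hypothesis names workload as one of three domains in which HL2 care is held to be equivalent to standard practice. The Statistical analysis paragraph says "The Wilcoxon-Mann-Whitney U test will be used to analyse TLX scores" and adds that within-subject comparisons will be made. Section 11a mentions questionnaires only to say that participants are kept apart while filling them in; it gives no time.

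**The concern.** Workload and anxiety belong to a condition: a participant has one level under standard care and another with the headset. Comparing them needs a score for each, taken close to the experience it describes. A single collection point after both scenarios cannot supply this for whichever condition came first. The participant must look back over the wash-out and the second scenario, and rates the first condition with the other in mind. For a state scale, which asks about feelings at the time, the mismatch is greatest.

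The setting makes retrospective self-rating more fragile. Participants know when they are wearing a headset. The recruitment wording in Appendix 2 tells them that the work looks at how the device can lower stress, and section 16f plans to explain its potential to ease the demands on staff. Someone rating both conditions together after hearing this may move the two scores apart to match expectation, or level them out. Either would distort the contrast that the hypothesis addresses. A first-condition score not taken at the time cannot be recovered later.

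**Working it through.** **Inputs (all from the protocol)**
- Participants: 30; scenarios: 60, with 30 per condition (section 10, Simulation study method; section 13a).
- Scenarios per participant: 2, in one session (section 10).
- Gap between scenarios: at least 1 hour (section 10).
- Time of questionnaires: study completion (section 10, Outcome measures).
- End of study: the final participant visit (section 6b).
- Duration of a scenario, and the size of any recall effect: not given.

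**1. The plan's own count.** 30 participants × 2 scenarios = 60, and 60 / 2 = 30 per condition. This agrees with the protocol.

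**2. How many ratings are affected.** Each participant has exactly one first scenario: 30 × 1 = 30 ratings, and 30 / 60 = 50% of all scenario ratings.

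**3. How long the recall is.** Time from the end of scenario 1 to the form = wash-out + duration of scenario 2. With a wash-out of at least 1 hour and a second scenario of some length, the delay exceeds 1 hour.

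**4. Does the meaning of study completion matter?** If it is the end of the participant's session, it falls after scenario 2. If it is the end of the study as in section 6b, it falls at the same time or later. On neither reading is there a rating before the second condition begins.

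**5. What randomised order does and does not remove.** Let τ be the true HL2 minus standard-care difference in a score. Let r_H be the shift when the HL2 scenario is the one recalled, and r_S the shift when standard care is. Leave other period effects aside.
- HL2 first: expected difference = τ + r_H.
- Standard care first: expected difference = τ − r_S.
- Average over equal-sized sequences: τ + (r_H − r_S)/2.

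If delay acts alike on both conditions (r_H = r_S = r), the average is τ, so the mean is unbiased. The individual differences are then τ + r in one sequence and τ − r in the other. This adds r² to their variance unless the analysis allows for period, so the contrast is blurred. If recall acts differently on the two conditions, as expectation about the device could cause, a bias of (r_H − r_S)/2 remains. If side-by-side rating stretches or shrinks the contrast by a factor k, both sequences give kτ, and balancing the order does nothing about it.

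The protocol gives no basis for values of r_H, r_S or k, so no numerical bias is put forward.

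**The case against.** The strongest reply is that the sentence was not meant as a schedule. It may only contrast questionnaires gathered on the day with videos rated later. Study completion is not defined per participant, and the forms are said to be in attachments that are not shown; these may tie each form to a scenario. The 30 and 30 scenarios and the planned within-subject comparisons also suggest that a score per condition was intended. This stands as a reason for moderate confidence. It does not remove the point: if completion after each scenario was intended, the sentence states the wrong time, and staff who follow it will collect the first score too late.

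A second reply is that order is randomised and the scenarios are counterbalanced, so recall delay falls on both conditions. This is right for delay alone, as step 5 shows. A reader might infer that TLX and STAI results could not be attributed to HL2 at all; that goes too far. What remains is bias that depends on the condition, and loss of precision.

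A reader might also infer that only one form per person is completed, that only the second condition is rated, and that the comparison therefore shrinks from 30 pairs to about 15 against 15, with a matching loss of power. The documents do not support this. Nowhere do they say that responses are taken once only or on one form. The unpaired test named for TLX could be run on such data, but the scenario counts and the within-subject comparisons fit two scores per person better (although the latter are described in terms of performance, not workload). With two forms at the end, all 30 pairs are kept.

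Finally, the reach is limited: these are secondary outcomes in a pilot whose stated purpose, in section 13e, is to inform a later power calculation.

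**Conclusion.** The point holds in a limited form. The protocol fixes a collection time that, if followed, gives no contemporaneous NASA-TLX or state-anxiety score for the first condition. It affects 30 of 60 scenario ratings, each recalled after more than 1 hour and after exposure to the other condition. The likely harm is a biased or blurred HL2 versus standard-care contrast in self-rated workload and anxiety, of a size that cannot be computed from the document. ICECAP, rated from video, is untouched, as are the other video-rated outcomes.

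This assumes that the sentence means what it says and that the attachments do not set a different time. No reduction in sample size or power is claimed. It is worth correcting before the first participant because workload is part of the hypothesis and the remedy is small.

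**What to change.** Replace the timing clause for participant responses in Outcome measures with wording such as:

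> NASA-TLX and STAI-state are completed immediately after each scenario, before the wash-out or any debrief; the HL2 usability questionnaire is completed after the HL2 scenario or at session end.

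The clause on later video rating can stay. If the attached forms already carry a scenario label or time, bring them into line with this sentence.

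The cost is one sentence and at most one additional completion of each form per participant (none if two sets at the end were already intended). The first set takes a few minutes after scenario 1 and fits into the interval of at least an hour already planned there. Section 10 describes the session both as a half-day and as at most 2 hours. Under the shorter figure only 2 − 1 = 1 hour is left outside the wash-out, so using the interval for the first set is also the economical choice. Baseline or trait STAI measurements may be useful, but they are not needed to cure this defect.

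### The tests named for the primary outcome and the main secondary outcomes are unpaired, although every participant supplies an observation under both conditions

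*Protocol*

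**What the plan says.** Protocol section 10, under the simulation study method, fixes the design: "The study will be conducted according to a randomised cross-over design". Each participant is randomised to a first condition and "will cross-over into the alternate group for the second scenario". The planned total is a "total of 60 clinical scenarios (30 as standard care, 30 as HL2 supported care"), from 30 people. The same section says that the two scenarios differ, and adds: "The order of the test scenarios will be counterbalanced to mitigate any learning effects".

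The statistical analysis paragraph, at the end of the outcome measures, then names the tests:

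- For the primary outcome (ICECAP), OTAS and completion time: "Independent two-sample t-tests will be calculated for normal continuous data, including ICECAP and OTAS scores, and time-to completion data".
- For cognitive load: "The Wilcoxon-Mann-Whitney U test will be used to analyse TLX scores".
- For adjustment: "Multivariate linear regressions will be calculated to control for potential confounders and to assess association".
- As a closing sentence: "Within subject comparisons will also be made to assess how the technology influences individual performance".

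The hypothesis in section 10 is one of equivalence between HL2-supported and standard care; no margin is given. Section 13e gives no power calculation, because no SD was available, and makes the purpose of the pilot to inform the power calculation of a later trial.

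**The concern.** The independent t-test and the Mann-Whitney test both treat the 30 HL2 values and the 30 standard-care values as coming from 60 unrelated people. Here the same 30 people appear on both sides. A person who makes few errors in one scenario will probably make few in the other. That shared component cancels out of the within-person difference, but the unpaired test leaves it in the error term.

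At stake is the inference on the primary outcome and on three further measures. The intervals for the device effect would not have their stated coverage, and the p-values would not have their stated size. The stated hypothesis makes this more awkward. A test tilted towards non-significance can be misread as support for equivalence, while the intervals that a proper equivalence assessment needs are too wide.

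This is not a matter of detail left to a later analysis plan. The protocol names a specific test for its primary outcome, and that test does not fit its own design.

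**Working it through.** **Inputs from the protocol.** 30 participants, two scenarios each: 30 × 2 = 60 scenarios, 30 per condition, which reproduces the stated total. The protocol gives no SD, correlation, effect size, alpha or margin, so there is no power figure to reproduce.

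**Assumptions (not in the protocol).** Equal SDs in the two conditions; normal data; two-sided 5% level; rho = 0.3, 0.5 or 0.7; a difference of 0.5 SD for power.

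**Standard errors, in SD units.**

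- Assumed by the independent t-test: √(2/30) = 0.258, whatever rho is.
- Correct for pairs: √(2(1 − rho)/30) = 0.216, 0.183, 0.141.
- Ratio: 1/√(1 − rho) = 1.20, 1.41, 1.83.

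**95% interval half-widths.** Unpaired: 2.00 × 0.258 = 0.52 SD (58 degrees of freedom). Paired: 2.05 × 0.216, 0.183 and 0.141 = 0.44, 0.37 and 0.29 SD (29 degrees of freedom).

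**Type I error and power**, by simulation of 30 pairs:

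| rho | SE ratio | True type I error, independent t | Type I error, paired t | Power at 0.5 SD, independent t | Power at 0.5 SD, paired t |
|---|---|---|---|---|---|
| 0.3 | 1.20 | 2.0% | 5% | 47% | 61% |
| 0.5 | 1.41 | 0.7% | 5% | 47% | 75% |
| 0.7 | 1.83 | 0.1% | 5% | 46% | 93% |

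The Mann-Whitney test behaves in the same way (type I error 1.8%, 0.7%, 0.1%), while the signed-rank test stays close to 5%. A two-sample t-test on period differences between the two sequences (15 against 15) has almost the same power as the paired t-test: 61%, 75%, 93%.

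**Outside this range.** At rho = 0 the independent t-test is right. At rho = 0.1 little is lost: type I error is about 4%, and power is 47% against 50%. At rho = −0.2 the direction reverses: the SE ratio is 0.91 and type I error is about 7%.

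**Equivalence.** Take an assumed margin of 0.5 SD, no true difference and two one-sided 5% tests. The chance of concluding equivalence is 46%, 70% and 93% with the paired analysis, and about 26%, 30% and 38% with the unpaired one.

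**The case against.** **The paragraph also plans within-subject comparisons.** This is true, so a reader who infers that the whole benefit of the cross-over is thrown away goes too far. It is lost for the named tests, not for everything that the plan foresees. But the sentence gives no method, outcome or priority, and it is worded as an addition. It does not displace the test named for ICECAP.

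**The t-test could be meant for period differences between sequences.** That would be a valid cross-over analysis. The text, however, applies the test to the ICECAP and OTAS scores themselves and lists within-subject comparisons separately, so this reading has no support.

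**The regressions might repair it.** A reader might equally infer the opposite: that they are ordinary regressions on 60 rows, without a participant term and without period or scenario. The protocol says neither. It lists no covariates and no error structure, so these features are unspecified rather than excluded, and such detail can properly sit in an analysis plan. No error rate for the regression can be charged to the protocol.

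**The error is conservative and its size is unknown.** This stands in part. With positive rho, no excess of false device effects arises, and with small rho the loss is minor. The SDs and the correlation needed for the later trial can be estimated from the data whichever test is run, so the stated purpose of the pilot is not defeated. Being conservative for a difference test is nevertheless no protection when the hypothesis is equivalence.

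**Conclusion.** Wrong as written. The independent t-tests for ICECAP, OTAS and completion time and the Mann-Whitney test for TLX do not fit the paired data that the protocol's own design produces, and nothing elsewhere in the document corrects this. Under the assumed correlations, the cost is intervals 1.2 to 1.8 times as wide as they need be, and a loss of about 14 to 47 percentage points of power for a 0.5 SD difference.

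The existence of the fault does not depend on rho, except in the special case of rho = 0; its size and direction do. The conclusion covers the four named measures. It does not extend to a claim that the regression is mis-specified, that period and scenario are left out of every analysis, or that no within-person analysis is planned.

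**What to change.** Rewrite the statistical analysis paragraph in section 10 as follows.

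1. For ICECAP, OTAS and completion time, make a within-participant cross-over analysis the primary one, and report the HL2-minus-standard difference with its 95% confidence interval. Either of these would serve:
   - a mixed model with a participant effect, device and period, plus scenario where the counterbalancing lets it be estimated, that is, where scenario order varies within each device order;
   - a two-sample t-test comparing within-participant period differences between the two sequences, where half the difference in means estimates the device effect.
2. For TLX, replace the Mann-Whitney test on raw scores with a paired or cross-over rank method, such as the signed-rank test or a rank-sum test on period differences between sequences. Only the latter allows for period.
3. State that any regression using both scenarios accounts for the participant.
4. Fold the closing sentence on within-subject comparisons into item 1, so that each outcome has one primary analysis.

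The cost is wording only: no further participants, data or measurements.

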## 11. Safety

### 11a. How will the safety of the research be managed?

All participants and study team members will follow both the Imperial College London and Imperial College Healthcare NHS Trust guidance on safe clinical practice during COVID-19. All participants will be asked to complete a screening questionnaire and will wear appropriate PPE when visiting the simulation lab as per local guidelines. The current version of the screening questionnaire in use at the Trust is provided in Appendix 1. These guidelines are subject to change and the current version will be strictly adhered to.

While performing simulations, full barrier PPE will be worn. Participants will be kept separated when completing questionnaires and there will be no congregation of staff. We will keep a register of attendees for tracking and trace purposes. The study will take place in a purpose-built clinical simulation lab at Imperial College London. All local health and safety policies and procedures will be adhered to throughout.

### 11b. Who is the named person taking responsibility for the overall safety of the research, and who will be responsible for day-to-day safety?

[name] – Chief Investigator

### 11c. How will the researchers conducting this study be made aware of:

- Their responsibilities for reporting any new safety issues which arise after the start of the project, and

## ii. Their responsibilities for reporting adverse events in the conduct of the project?

The scientific committee will provide clear guidance to all researchers on safety reporting mechanisms and their responsibilities. These will be provided in a written information sheet and they will be reinforced during all simulation briefings and debriefings. The greatest risk will be the transmission of COVID-19 between participants. We will ensure that this is incorporated into the briefing and that all members of the team have a clear reporting line in the event of a positive test as per Imperial College London / Imperial College Healthcare NHS Trust policies and procedures. We will minimise the number of participants together at any one time and will ensure that all safe working practice regulations (e.g., appropriate social distancing, following maximum room capacity rules, use of PPE) are strictly adhered to so that the study is conducted in a "COVID secure" manner as per local rules and regulations.

